## Abstract

**Background:**

Stress urinary incontinence (SUI) is a prevalent condition among adult women, significantly impairing quality of life. Patients with SUI often exhibit abnormal pelvic floor muscle function, which can be comprehensively assessed using surface electromyography (sEMG) and transperineal ultrasound (TPUS). Electroacupuncture (EA) is an effective treatment for SUI, and multiple studies have confirmed its clinical efficacy; however, objective evidence regarding its impact on pelvic floor muscle function remains limited. This study aims to evaluate the clinical efficacy of EA applied to lower abdominal acupoints for SUI and to explore its impact on pelvic floor function, thereby providing mechanistic insights into EA's therapeutic effect on mild to moderate SUI.

**Methods:**

This is a randomized, single-blind trial with a 1:1 allocation ratio. A total of 64 participants will be enrolled. Following screening, eligible female patients with SUI will be randomly allocated to either the EA group (*n* = 32) or the sham EA group (*n* = 32), receiving EA or sham EA treatment, respectively. The intervention period will last 6 weeks. The primary outcome is the change in urine leakage, measured by the 1-hour pad test, from baseline to week 6. Secondary outcomes include: the incontinence episode frequency (IEF); the International Consultation on Incontinence Questionnaire-Short Form (ICIQ-SF) score; SUI severity; weekly urine pad usage; participants' self-assessment of therapeutic effect; pelvic floor muscle sEMG parameters; TPUS measurements; discomfort during treatment assessed by a Visual Analog Scale (VAS); participants' acceptability; and intervention-related adverse events.

**Conclusion:**

By comprehensively evaluating symptom improvement, temporal effects, and pelvic floor functional changes following EA treatment for SUI, this study aims to systematically elucidate the therapeutic effects of EA and its mechanism of action on the pelvic floor. The findings are expected to provide robust evidence to support the clinical application of EA for SUI.

**Clinical Trial Registration:**

https://itmctr.ccebtcm.org.cn/mgt/project/view/-6004709097458762939, identifier ITMCTR2024000151.

## Introduction

1

Stress urinary incontinence (SUI) is a highly prevalent condition among adult women. The International Continence Society (ICS) defines SUI as the complaint of involuntary urine leakage upon effort or exertion, such as laughing, sneezing, or coughing (1). Epidemiological data indicate a high incidence of SUI. The median global prevalence of urinary Incontinence in women is 27.6% (range: 4.8%–58.4%), with SUI accounting for over 50% of cases (2). SUI severely impacts patients’ social activities, physical exercise, and sexual life, leading to psychological issues such as anxiety and depression, as well as social isolation. Consequently, it significantly reduces quality of life (3) and imposes a substantial economic burden on society. SUI is closely associated with impairments in pelvic floor structure and function. Patients often exhibit a weakened urethral mucosal seal, inadequate urethral sphincter and pelvic floor muscle strength, laxity of fascia and ligaments, and other functional or structural abnormalities of the pelvic floor. Insufficient pelvic floor support can lead to hypermobility of the bladder neck and proximal urethra. When abdominal pressure increases, bladder pressure may exceed urethral closure pressure, resulting in urine leakage (4).

Current treatment options for SUI primarily include behavioral interventions, pelvic floor muscle training (PFMT), biofeedback, pharmacotherapy, and surgery (5). PFMT is the first-line treatment for mild to moderate SUI; however, it requires patients to adhere to 3–6 months of training to achieve potential efficacy. It also demands professional guidance and supervision, which can challenge patient compliance (6). Electroacupuncture has gained recognition as a promising non-pharmacological treatment for SUI. Studies have demonstrated its efficacy in reducing urine leakage and improving quality of life (7, 8). Acupuncture at lower abdominal acupoints is widely employed in SUI treatment (9). Notably, it has been shown to immediately reduce the mobility of the bladder neck and proximal urethra, thereby improving pelvic floor function (10).

The therapeutic mechanisms of electroacupuncture for SUI are considered to involve multiple pathways. Firstly, it may modulate spinal and central reflex arcs to enhance urethral sphincter control and improve pelvic floor muscle function (7, 11). Secondly, it is thought to promote local blood circulation and nutrient supply, thereby aiding in the recovery of muscle elasticity and strength (12, 13). Additionally, electroacupuncture may facilitate tissue repair by modulating collagen metabolism in pelvic supportive structures (14, 15). These multifaceted actions highlight its potential as a comprehensive therapy for SUI. Despite its established clinical efficacy, significant gaps remain in the objective characterization of EA's impact on pelvic floor physiology. Many prior studies lack a systematic integration of objective functional and structural assessments. Furthermore, when EA is combined with pelvic floor muscle training, the specific effects attributable to EA alone are often unclear (7, 16).

Therefore, this sham-controlled trial aims to rigorously evaluate the efficacy of EA as a monotherapy for SUI and to investigate its specific effects on pelvic floor muscle function and structure, thereby providing novel mechanistic insights.

## Methods and analysis

2

### Study design

2.1

This study is a randomized, single-blind, controlled trial. The study will be conducted in the acupuncture department of Yueyang Hospital of Integrated Traditional Chinese and Western Medicine, Shanghai University of Traditional Chinese Medicine, China. The study protocol has been approved by the Medical Ethics Committee of Yueyang Hospital of Integrated Traditional Chinese and Western Medicine, Shanghai University of Traditional Chinese Medicine (Approval No. 2024-039) and is registered with the International Traditional Medicine Clinical Trial Registry (ITMCTR2024000151). The protocol adheres to the Standard Protocol Items: Recommendations for Intervention Trials (SPIRIT) 2013 guidelines (17). The study flowchart is presented in Figure 1, and the enrollment, interventions, and assessments schedule is outlined in Table 1.

**Figure 1 F1:**
[figure not shown]
Flowchart. SUI, stress urinary Incontinence; IEF, incontinence episode frequency; sEMG, surface electromyography; ICIQ-SF, International Consultation on Incontinence Questionnaire-Short Form; AEs, adverse events.

**Table 1 T1:** Schedule of recruitment, interventions and assessments.

Study period	Enrolment	Intervention					
Time point	Week 0	Week 1	Week 2	Week 3	Week 4	Week 5	Week 6
Inclusion/exclusion criteria	X						
Sign informed consent	X						
Baseline information collection	X						
Randomization	X						
Intervention							
Electroacupuncture		X					
Sham electroacupuncture		X					
Primary outcome							
Urine leakage	X						X
Secondary outcomes							
Incontinence episode frequency	X		X		X		X
ICIQ-SF	X		X		X		X
Severity of SUI	X		X		X		X
Weekly usage of urine pads	X		X		X		X
Participants’ self-evaluation of therapeutic effects			X		X		X
Pelvic floor surface Electromyography	X						X
Transperineal ultrasound	X						X
Safety evaluation		X	X	X	X	X	X
Evaluation of discomfort during treatment		X		X			
Participants’ acceptability evaluation		X		X			

SUI, stress urinary incontinence; ICIQ-SF, International Consultation on Incontinence Questionnaire-Short Form.

### Participant and consumer involvement

2.2

The inclusion criteria are as follows: diagnosis of mild or moderate SUI in women (18, 19); age between 40 and 75 years. All participants will provide written informed consent before enrollment. Exclusion criteria include: urge urinary Incontinence, mixed urinary Incontinence, or overflow urinary Incontinence; history of surgical treatment for urinary Incontinence or pelvic floor surgery; genital prolapse of stage II or greater; symptomatic urinary tract infection; postvoid residual urine volume > 30 mL; maximum urinary flow rate < 20 mL/s; inability or limited ability to walk, climb stairs, or run; continuous use of medications affecting bladder function or ongoing specialized treatment for SUI; severe cardiac, cerebral, hepatic, renal, hematopoietic system, or psychiatric diseases; diabetes mellitus, multiple system atrophy, cauda equina lesions, or spinal cord pathologies; pregnancy, lactation, or intention to become pregnant during the trial period; presence of a cardiac pacemaker, metal allergy, or severe needle phobia. The withdrawal criteria are as follows: experience of severe complications or other serious illnesses that preclude continued participation; participant's request to withdraw from the trial. Data will be analyzed according to the intention-to-treat (ITT) principle.

### Operator qualifications and standardization

2.3

Two licensed acupuncturists will perform all acupuncture procedures, each with at least five years of clinical experience and a nationally recognized acupuncture practice certificate. Before the study commencement, all operators will undergo a one-week standardized training program covering acupoint localization, needle insertion depth, manipulation techniques, and safety protocols. Inter-operator consistency will be assessed through simulated treatment sessions, requiring at least 85% agreement on key parameters (e.g., acupoint localization accuracy, insertion depth, and manipulation frequency).

### Interventions

2.4

Before treatment, participants will be instructed to empty their bladders and assume a supine position. All treatments will be administered following skin disinfection. Disposable sterile acupuncture needles (Guizhou Andi Pharmaceutical Equipment Co., Ltd.; sizes: 0.30 mm × 75 mm and 0.30 mm × 25 mm) will be used. Participants will receive three weekly treatment sessions (on alternate days), 30 min per treatment session, totaling 18 sessions over 6 weeks.

#### EA group

2.4.1

Sterile adhesive pads will be positioned at the acupoints Guanyuan (RN4), Zhongji (RN3), and Dahe (KI12) (Figure 2). A 0.30 mm × 75 mm needle will be inserted through the pad at an angle of 30° to 45° toward the perineum, reaching a depth of 40–50 mm. The needle will then be rotated gently and evenly at approximately 60 revolutions per minute with an amplitude of 180°–360° to elicit the *deqi* sensation, characterized by soreness, numbness, or distension radiating toward the bladder, perineum, or urethra. Subsequently, electroacupuncture stimulation will be applied using a continuous wave at 50 Hz. The current intensity will be set between 1 mA and 5 mA and gradually increased until a slight, painless tremor is observed in the tissues surrounding the acupoint. One pair of electrodes will connect the left KI12 and RN3 acupoints, and another pair will connect the right KI12 and RN4 acupoints.

**Figure 2 F2:**
[figure not shown]
Locations of acupoints. RN3: Zhongji; RN4: Guanyuan; KI12: Dahe.

#### Sham EA group

2.4.2

Sterile adhesive pads will be placed at the same acupoint locations (RN3, RN4, KI12). A blunted tip needle (0.30 mm × 25 mm) will be placed onto the pad at a 30 °–45 ° angle without penetrating the skin. The *deqi* sensation will not be elicited (Table 2). The electroacupuncture apparatus will be identical in appearance to that used in the EA group, but will have its internal circuits disconnected, ensuring no current is delivered. The device display will indicate 50 Hz and 1–5 mA settings, but participants will not perceive any electrical stimulation. Electrodes will be connected superficially in a comparable configuration: between the left KI12 and RN3, and the right KI12 and RN4 acupoints.

**Table 2 T2:** Locations and manipulations of acupoints.

Acupoint name	Location description	Manipulation details (EA group)	Manipulation details (sham EA group)
Zhongji (RN3)	On the anterior midline, 4 cun inferior to the umbilicus.	Following skin disinfection, a sterile filiform needle (0.30 mm × 75 mm) is inserted at each acupoint at a 30 °–45 ° angle toward the perineum to a 40–50 mm depth. Manual needle manipulation is performed to elicit the *deqi* sensation. Subsequently, electrodes are connected (left KI12-RN3 and right KI12-RN4) and electrical stimulation is applied (continuous wave, 50 Hz, 1–5 mA, adjustable to a painless muscle twitch).	Following skin disinfection, a sterile blunted tip needle (0.25 mm × 25 mm) is placed at the same angle onto the pad, but does not penetrate the skin. No manipulation is performed, and *deqi* is not elicited. The sham device, identical in appearance, is connected similarly but delivers no current.
Guanyuan (RN4)	On the anterior midline, 3 cun inferior to the umbilicus.		
Dahe (KI12)	0.5 cun lateral to the anterior midline, 4 cun inferior to the umbilicus.		

Both interventions will be administered in accordance with the methods described by Liu et al. (7)and the SHARE guidelines (20).

### Outcome measures

2.5

#### Primary outcome

2.5.1

The change in urine leakage, as measured by the 1-hour pad test, from baseline to week 6. The test procedure will follow: the participant will wear a pre-weighed pad, drink 500 mL of water within 15 min, and perform a series of activities. These activities include walking for 30 min (which incorporates stair climbing), repeatedly sitting down and standing up, vigorous coughing, running in place, bending to pick up a small object from the floor, and washing hands under running water. The pad will then be reweighed to quantify the urine leakage (21). The assessment will be postponed or rescheduled if the participant is menstruating or experiences an episode of severe coughing.

#### Secondary outcomes

2.5.2

Incontinence episode frequency (IEF): Mean IEF over 72 h will be recorded in a bladder diary. Assessments will be performed at baseline, week 2, week 4, and week 6. Change from baseline will be calculated.ICIQ-SF score: The International Consultation on Incontinence Questionnaire-Short Form (ICIQ-SF) will be used to retrospectively evaluate the frequency, volume of Incontinence, and impact on quality of life over the preceding four weeks. The validated Chinese version will be administered (22). The questionnaire includes three scored items (assessing the frequency of urinary Incontinence, the amount of leakage, and the degree of interference with quality of life) and one non-scored self-diagnosis item (used to provide additional qualitative information). The total score ranges from 0 to 21, with higher scores indicating greater symptom severity (23). Scores will be collected at baseline, week 2, week 4, and week 6.Severity of SUI: The overall severity of urinary leakage was evaluated based on patient-recorded 72-hour bladder diaries, which documented episodes occurring under normal circumstances (i.e., excluding vigorous coughing, exercise, or heavy lifting). Severity was categorized as follows: Mild: leakage of a few drops; Moderate: leakage that partially soaks a pad; Severe: leakage that thoroughly soaks a pad in a single episode. The most severe episode encountered is recorded (7). To enhance objectivity, all participants will be provided with standardized urinary pads (Brand: TENA, Size: 375 mm × 135 mm, Absorption: 100 mL). Additionally, we will record the 72-hour cumulative pad weight (difference between wet and dry weight using a precision scale  ± 0.1 g) as a quantitative measure of leakage severity. Participants can store pads in labelled zipper bags for weighing, reporting daily and 72-hour total leakage amounts. The severity of stress urinary incontinence will be assessed by trained outcome assessors who are blinded to the participants' group allocation. Assessments will be conducted at baseline, week 2, week 4, and week 6.Weekly usage of urine pads: Participants will maintain a daily diary to record the number of pads used. The change from baseline in the average number of pads used per 2 weeks will be calculated. To provide objective supplementation, we will also derive two metrics from standardized pad weights: weekly total pad weight (g) and mean leakage per pad (g/pad). Provide participants with identical pads and labeled bags. Each pad's dry weight should be pre-measured and labeled at the center (ID and tare), with participants returning only the wet pads. All weighings should be performed on the same scale, by the same trained personnel, within a fixed time window, with daily calibration logs maintained. Data will be collected at baseline, week 2, week 4, and week 6.Participants' self-evaluation of therapeutic effects: This subjective satisfaction rating assesses participants’ perception of treatment benefit. Participants will be asked, “Has the treatment helped you control your urine leakage?” Responses will be rated on a 4-point scale: 0 = not helpful at all; 1 = slightly helpful; 2 = moderately helpful; 3 = very helpful (7). Evaluations will be performed at week 2, week 4, and week 6.Pelvic floor muscle surface EMG (sEMG): Parameters will be assessed at baseline and week 6 using the standard Glazer protocol with participants in the lithotomy position (24). The evaluated parameters include: pre-resting baseline tone; amplitude of phasic (Type II fast-twitch) muscle contractions (calculated as the mean amplitude of five rapid contractions); amplitude of tonic (Type I slow-twitch) muscle contractions (calculated as the mean amplitude of five 10-second sustained contractions); endurance of Type I muscles (mean amplitude during a single 60-second sustained contraction); and post-resting baseline tone. Changes in the EMG amplitude for both Type I and Type II muscle fibers from baseline to week 6 will be analyzed.Transperineal ultrasound (TPUS): TPUS assessments will be performed at baseline and week 6 with participants in the lithotomy position. Parameters to be measured include: bladder neck mobility, urethral rotation angle, retrovesical angle (posterior bladder angle), position of the lowest point of the bladder (bladder neck descent), urethral funneling, and the type of cystocele (bladder prolapse) at rest and during the Valsalva maneuver (25).Evaluation of discomfort during treatment: Discomfort experienced during the acupuncture session will be evaluated using a Visual Analog Scale (VAS) ranging from 0 cm (indicating no discomfort) to 10 cm (indicating severe discomfort). The average VAS score recorded within 5 min after the first and ninth treatments will be used for analysis. If a score from one session is missing, the available score from the other session will be used (7).Participants' acceptability evaluation: The acceptability of the treatment procedure will be rated on a 5-point scale: 0 = very difficult to accept; 1 = somewhat difficult to accept; 2 = acceptable; 3 = easy to accept; 4 = very easy to accept. The average score will be calculated within 5 min after the first and ninth treatments. If a score from one session is unavailable, the score from the remaining session will be utilized (7).

#### Safety evaluation

2.5.3

All adverse events (AEs) will be recorded in the Case Report Form (CRF). Details to be documented include the date of onset and resolution, severity, relationship to the intervention, and measures taken for management. Treatment-related AEs may include, but are not limited to: dizziness, fainting, abscess formation, subcutaneous hematoma, local infection, and other discomforts such as fatigue or palpitations. Any occurring AEs will be managed appropriately. Serious AEs will be reported immediately to the Data and Safety Monitoring Board (DSMB), which will assess their relatedness to the intervention and recommend continuing the study. The frequency and percentage of participants experiencing AEs in each group will be calculated.

### Data analysis

2.6

#### Sample size calculation

2.6.1

The sample size was calculated for a superiority trial comparing two independent means, with a 1:1 allocation ratio, a two-sided *α* of 0.05 (*Z_α/2_* = 1.96), and a power (1-*β*) of 80%(*Z_β_* = 0.84). Based on data from our previous research, the anticipated change in urine leakage (1-hour pad test) from baseline to week 6 was used for calculation: EA group mean *μ_t_* = 8.59 g, Sham EA group mean *μ_c_* = 4.81 g, standard deviation *σ* = 4.76 g, superiority margin *Δ* = 0. Using these parameters, the calculated sample size required per group was 25. Accounting for an estimated dropout rate of 20%, 64 participants (32 per group) will be required (26, 27).$$n=\frac{2{\left(Z_{\alpha /2}+Z_{\beta }\right)}^{2}\;\times \sigma^{2}}{{\left(\mu_{t}\text{-}\mu_{c}\text{-}\Delta \right)}^{2}}$$

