#### Statistical methods

2.6.4

Statistical analyses will be performed on the intention-to-treat (ITT) population and the per-protocol (PP) population. For the ITT analysis, missing data will be handled using multiple imputation by chained equations (MICE). All statistical analyses will be conducted using SPSS software (version 26.0; IBM Corp.). Results will be presented with 95% confidence intervals, and a two-sided *P* value of less than 0.05 will be considered statistically significant. Continuous variables normally distributed will be summarized as mean ± standard deviation, while those with a non-normal distribution will be summarized as median and interquartile range (IQR). Comparisons of continuous variables between the two groups will be performed using the independent samples *t*-test (for normal data) or the Mann–Whitney *U*-test (for non-normal data). Categorical data will be described as frequencies and percentages, and comparisons between groups will be made using the appropriate Chi-squared test or Fisher's exact test. For longitudinal analysis of outcomes measured over time, generalized estimating equations (GEE) or linear mixed-effects models will be employed to account for correlations within subjects and to examine time-by-group interaction effects. In secondary analyses, we will explore potential effect modification by menopausal status by including an interaction term in our statistical models. For the exploratory secondary outcomes, interpretation will focus on effect sizes and confidence intervals rather than unadjusted *P* values to avoid inflation of type I error due to multiple comparisons. No formal multiplicity adjustment will be applied to secondary endpoints.

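### The t-test named for the analysis has slightly less than the stated 80% power at the planned size (78.6% with 25 completers per arm); adjusting for baseline leakage can recover this without more patients

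*Protocol article*

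**What the plan says.** Section 2.6.1 (Sample size calculation) of the protocol article opens: "The sample size was calculated for a superiority trial comparing two independent means, with a 1:1 allocation ratio". It sets two-sided alpha at 0.05 and power at 80%, entered as the normal quantiles 1.96 and 0.84. The anticipated changes in 1-hour pad-test leakage from baseline to week 6 are "EA group mean *μ_t_* = 8.59 g" and "Sham EA group mean *μ_c_* = 4.81 g", with a common standard deviation of 4.76 g and a margin of zero. From these, "the calculated sample size required per group was 25". The section continues: "Accounting for an estimated dropout rate of 20%, 64 participants (32 per group) will be required".

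Section 2.6.4 (Statistical methods) names the tests: "Comparisons of continuous variables between the two groups will be performed using the independent samples" t-test when the data are normal, and by the Mann–Whitney test when they are not. Section 2.6.2 (Randomization) specifies simple randomization. Table 1 schedules the pad test at week 0 and week 6. In the Discussion, the limitations paragraph says the sample size satisfies the basic requirements for the primary outcome.

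**The concern.** The sizing formula and the named test do not quite match. The formula uses normal quantiles, as if the standard deviation were known. The t-test estimates it from about 50 participants, so its critical value is a little larger than 1.96 and its power a little lower. Because 24.86 rounds up to 25, rounding leaves almost no slack to absorb the difference.

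What is at stake is the accuracy of the stated power, on which the Discussion relies when it calls the sample size adequate for the primary outcome. The validity of the comparison is not affected. The same passages also leave a free gain unused: baseline leakage is measured in every participant, but the named test for the primary outcome does not adjust for it.

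**Working it through.** **Inputs** (all from section 2.6.1): mean changes 8.59 g and 4.81 g, SD 4.76 g, margin 0, quantiles 1.96 and 0.84, dropout 20%, 32 enrolled per arm.

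**Step 1: reproduce the stated figures.**
- Difference = 8.59 − 4.81 = 3.78 g; standardised d = 3.78/4.76 = 0.794.
- n = 2 × (1.96 + 0.84)² × 4.76² / 3.78² = 2 × 7.84 × 22.658 / 14.288 = 24.86, so 25 per arm.
- 25/(1 − 0.20) = 31.25, so 32 per arm, 64 in total.

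Both figures reproduce. By the formula's own normal approximation, power at 25 per arm is 80.2%.

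**Step 2: power of the t-test on the same inputs.** With n completers per arm, the noncentrality is d × √(n/2), on 2n − 2 degrees of freedom. At n = 25 this is 0.794 × √12.5 = 2.81 on 48 degrees of freedom, and the critical value is 2.011 instead of 1.96.

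| Completers per arm | t-test power |
|---|---|
| 25 | 78.6% |
| 25.6 (= 32 × 0.8, expected) | 79.5% |
| 26 | 80.2% |
| 32 (no dropout) | 87.8% |

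The t-test therefore needs 26 completers per arm. Carried through the same dropout allowance, 26/0.8 = 32.5, so 33 per arm or 66 in total, two more than planned.

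**Step 3: allow for chance in dropout and allocation.**
- Arms fixed at 32, each participant dropping out independently with probability 0.2: average power 79.2%.
- 64 participants allocated by simple randomization, with the same dropout: average power about 78.6%, 5th to 95th percentile about 73% to 83%.

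The second figure includes chance imbalance in arm sizes, which the calculation in section 2.6.1 does not consider and which is separate from the choice of quantiles.

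**Step 4: baseline adjustment.** If baseline leakage and the change in leakage correlate r, adjustment reduces the residual SD by the factor √(1 − r²), so the effective standardised difference becomes 0.794/√(1 − r²). At 25 per arm:

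| Assumed r | Effective d | Power |
|---|---|---|
| 0.2 | 0.810 | 80.2% |
| 0.3 | 0.832 | 82.2% |
| 0.5 | 0.917 | 88.8% |

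The document gives no correlation, so these rows show a range and are not predictions. Charging one degree of freedom for the covariate changes each figure by less than 0.1 point.

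**The case against.** The strongest reply is that nothing in section 2.6.1 is miscalculated. It prints a standard formula and all of its inputs, and the answer and the dropout allowance are both right. That stands. A reader might infer an arithmetic error from the 78.6%. The document does not support that reading: the difference comes from an openly stated approximation.

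A second reply is that the gap is smaller than the uncertainty in the inputs. That also stands. At 25 per arm the t-test reaches 80% if the SD is 4.67 g instead of 4.76 g, or the difference 3.85 g instead of 3.78 g, about 2% either way. A 10% error in the SD moves power to about 86% or 71%. With dropout below 20% the power can exceed 80%.

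A third concerns the Mann–Whitney test. A reader might infer that it too falls short, because with normal data it has about 76% power at 25 per arm. But section 2.6.4 uses it only when the data are not normal. In simulations with the same mean shift and SD it had about 88% power under a gamma shape and 94% under a lognormal shape. Those shapes are assumed, others could behave differently, and the document gives none. No shortfall is shown for that test, and the 76% figure does not belong in the protocol.

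What survives is narrow. For the t-test, the approximation changes the integer answer from 25 to 26, and the stated 80% is not quite reached at the planned dropout.

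**Conclusion.** The point holds as a minor one. On the protocol's own means and SD, the named t-test misses the stated 80% by about 1.4 points at 25 completers per arm, by 0.5 point at the expected 25.6, and by about 1.4 points on average under simple randomization with random dropout. This assumes normal data, equal SDs, 20% dropout, and information roughly equal to that in the completers; the multiple imputation planned for the intention-to-treat analysis was not modelled.

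It would go too far to call the trial underpowered or the Discussion's statement about sample size false: a nominal 80% that is really about 79% does not support either. The more useful conclusion is that the baseline measurement already planned can make up the difference, provided it correlates with change by about 0.2 or more.

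**What to change.** Keep 64 participants. In section 2.6.4, name as the primary analysis an analysis of covariance of week-6 pad-test leakage (or of its change) with treatment group and baseline leakage as terms. The estimated group difference is the same for either outcome. In section 2.6.1, state the power under the baseline correlation that is assumed, and mark it as an assumption or support it from the sponsor's earlier data.

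If the unadjusted t-test is kept, restate the power as about 79% at the planned dropout and give no separate figure for the Mann–Whitney test.

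The cost is one or two sentences. No patients, visits or measurements are added, because Table 1 already schedules the baseline pad test. Adjustment uses one degree of freedom, which is negligible even if the correlation proves to be near zero. Keeping the t-test makes the stated power slightly less favourable.
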